#### Sampling

2.5.2

The sampling method will be done in a convenience method. Following the receipt of authorization from the Ethics Committee of Mazandaran University of Medical Sciences, the researcher registered the project in the Iranian Clinical Trial Registration Center, received its code, attended and presented a letter of introduction, and went to midwifery and gynecology offices in Tehran. In the first stage, the call will be announced through the offices; qualified people will be invited to take part in the study if they wish. Then, a list of qualified people will be prepared, and all the people who are eligible and have declared their preparation will be listed with a code (instead of specifications) in an Excel sheet.

### Random Allocation

2.6

In this study, the random blocking method will be utilized for the random allocation of samples in the intervention and control groups, based on marital status (single and married) and BMI (< 20, 20–25, and > 25). For this purpose, double blocks will be considered. The two possible blocks are TC and CT, where T stands for the intervention group, and C stands for the control group. Numbers will be generated randomly (with the RANDBETWEEN command in Excel software and ranges 1 and 2), and according to the production values of one of the blocks (for production number 1 CT block, for production number 2 TC blocks) will be selected and samples will be allocated. For instance, two married women with a body mass index of 20–25 have been referred, one assigned to the intervention group and the other to the control group. In Excel software, between numbers one and two, assuming the number two is selected randomly. Therefore, these two people are assigned to the TC block. Accordingly, these two people are assigned to refer to this block in order. The first person enters the intervention group, and the second person enters the control group. Now, if the number one is chosen, these two people will be assigned to the CT block [43].

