### Blinding

2.7

It will be impossible to keep participants blind during the intervention process, as a result of the nature of the intervention [44]. Blinding will be done at the assessor level [45]. In this way, after concluding the work, the research colleague hands over the questionnaires to the samples, and after completing the questionnaire, a box will be placed there, and the participants will put the completed questionnaire in the box. Groups are named A and B. The statistical analyst is also blinded, and at the end of the analysis, the coded groups will be identified [44, 45, 46]. Figure 1 is the CONSORT flow diagram and includes the calculation of the numbers of eligible, screened, enrolled, and analyzed participants.

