### Limitations

2.16

Our research might encounter various constraints. Since it is a public study, participants are aware they are engaging in an intervention entitled the Effect of Hypnotherapy on the Resilience of Women with PCOS, and bias is probable in the research outcomes. Subsequently, a random assignment of participants can help attain equilibrium in sociodemographic traits. One of the limitations of this study was the relatively short follow‐up period of 4 weeks. This duration is chosen due to the challenges posed by the COVID‐19 pandemic, during which the study will be conducted. Extending the follow‐up period beyond 4 weeks risks a significant loss to follow‐up due to the uncertainty and constraints experienced by participants during the pandemic. However, we acknowledge that a longer follow‐up period would provide more robust insights into the sustainability of the intervention's effects. Future studies are recommended to include longer follow‐up periods to evaluate the long‐term impact and efficacy of hypnotherapy in improving resilience and other psychological outcomes in women with PCOS. Another drawback of this study is the reliance on self‐reporting tools, and the potential for memory mistakes, ambiguity, sociocultural issues, and personal biases influencing the outcomes is unavoidable. The consultative nature of the intervention and the non‐blinding and concealment of the allocation status of the participants from the researcher's point of view will make performance bias possible in the present study. Last but not least, the possibility of a placebo or confounding effect remains in this protocol since participants in the experimental group receive significantly more interaction with the clinical team compared to those in the control group.

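### Fixed blocks of two in an open-label trial leave up to half of allocations predictable unless both women of a pair are enrolled before the draw

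*Protocol article*

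**What the plan says.** Section 2.6 (Random Allocation) stratifies "based on marital status (single and married) and BMI", which has three categories, so there are six strata. Within a stratum, "double blocks will be considered. The two possible blocks are TC and CT", T being the intervention arm and C the control arm. The choice between the two blocks is made in Excel: "Numbers will be generated randomly (with the RANDBETWEEN command in Excel software and ranges 1 and 2". Assignment within the block follows order; when TC is drawn, "The first person enters the intervention group, and the second person enters the control group". The worked example starts from two women of the same stratum who have both already been referred.

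Section 2.7 (Blinding) states: "It will be impossible to keep participants blind during the intervention process". Its blinding covers the assessor and the analyst. Section 2.9.2 (Data Management) says that the study coordinator, who documents recruitment, is not blind to the randomisation. Section 2.5.2 (Sampling) describes convenience sampling and a coded list of eligible, willing women, without saying that the list is closed before allocation begins. Section 2.10 (Interventions) hands out the questionnaires after allocation, and Table 1 places their first completion in the first hypnotherapy session. Section 2.16 (Limitations) names non-blinding and "concealment of the allocation status of the participants", from the researcher's side, as a source of performance bias.

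**The concern.** A block of two has no randomness left after its first member. In an open-label trial the first member's arm becomes visible, so anyone who sees past allocations in a stratum and knows the block rule knows what the next woman in that stratum will receive. With convenience sampling there is room to decide whom to approach next, or in what order.

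At stake is selection bias at entry, which randomisation is meant to exclude. All outcomes are self-reported and may depend on motivation and expectation, so arms that differ in these respects at entry could show a difference that looks like a treatment effect.

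**Working it through.** **Inputs.** From Section 2.6: block size 2, 1:1 allocation, 2 × 3 = 6 strata. From Section 2.5.1: N = 56; control 48.17 (SD 20.61); intervention 69.80 (SD 23.38); type 1 error 0.05; power 0.90; 20% attrition. Assumed, because the article gives no figures: stratum sizes (equal, or skewed with shares of 3%, 12%, 20%, 4%, 21% and 40%) and the size of any steering.

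**The plan's own figure.** Difference = 69.80 − 48.17 = 21.63. Pooled SD = √((20.61² + 23.38²)/2) = 22.04. With a two-sided test, n per group = 2 × (22.04 × (1.960 + 1.282)/21.63)² = 21.8, so 22. Then 44/0.8 = 55, rounded to 56. The sample size reproduces, and this point does not affect it.

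**Predictability in a single sequence.** The first member of each pair is a fair coin and the second is certain.
- Certain: 1/2 of 56 = 28.
- Expected correct guesses: (0.5 + 1)/2 = 75%.

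**Allowing for six strata.** A stratum with an odd count ends on an unpaired woman. If about half of the six strata end odd, 3 women are unpaired.
- Certain: (56 − 3)/2 = 26.5, and 26.5/56 = 47%.
- Correct guesses: (26.5 + 0.5 × 29.5)/56 = 41.25/56 = 74%.

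Simulation gives the same result for equal and skewed strata (26.5 certain, 74% guessed).

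**Alternatives.** Simulated for 56 women in six strata. The guesser knows the permitted block sizes and all earlier allocations in the stratum.

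| Block sizes | Certain allocations | Share certain | Correct guesses |
|---|---|---|---|
| 2, fixed | 26.5 | 47% | 74% |
| 4, fixed | 16.2 | 29% | 69% |
| 4 and 6, random | 3.0 to 3.3 | 5% to 6% | 67% |
| 2, 4 and 6, random | 1.8 | 3% | 68% |

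**Illustrative bias.** Suppose all 28 known slots, 14 per arm on average, are filled by women s SD better in the hypnotherapy arm and s SD worse in the control arm. Each arm mean moves by s/2 in opposite directions, so the difference moves by s/2 + s/2 = s SD.
- s = 0.1: 0.1 × 22.04 = 2.2 points, or 10% of 21.63.
- s = 0.25: 0.25 × 22.04 = 5.5 points, or 25% of 21.63.

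With 26.5 known slots instead of 28, multiply by 26.5/28 = 0.946, giving about 2.1 to 5.2 points. These are shifts before any baseline adjustment.

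**The case against.** The strongest reply is that the article's own example has both women referred before the draw, and one draw then fixes both. With the coded list in Section 2.5.2, this can be read as listing willing women first and allocating them in pairs. On that reading the second arm is not known when she is enrolled, and steering is blocked. The reading is fair, so it cannot be said flatly that every second allocation is known in advance. But the passage is an example. No section requires the first woman to be held until a second is irrevocably enrolled, or closes the list before allocation starts.

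A reader might also infer that there is no concealment at all, that the draw is made live by the recruiter, or that the hypnotherapist controls entry. The article does not say when the numbers are generated, who holds them or who enrols, and a full protocol that is not shown may say so. Nor does Section 2.16 concede selection bias: it draws only performance bias, which concerns conduct after allocation.

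The analysis gives some protection. Section 2.13 plans repeated measures ANOVA or mixed models that include the pre-intervention score, and Section 2.15 plans adjustment for confounders that differ. A stable difference in resilience at entry would be at least partly removed. That cannot be relied on, however, because the baseline questionnaires follow allocation and could themselves be affected by knowing the arm. Motivation and expectation are not listed as measured.

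Finally, larger varied blocks lower overall guess accuracy only from 74% to about 67%. This is true, and it is why block size alone is not a sufficient remedy.

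**Conclusion.** The point holds conditionally. The fixed block size of two, its contents and the in-order assignment are stated rules, so the weakness does not rest on missing detail. If pairs are not irrevocably enrolled before the draw, up to 28 of 56 allocations (about 26.5, or 47%, with six strata) are certain and about 74% to 75% can be guessed by anyone who sees earlier allocations in the stratum. The open-label design and the unblinded coordinator make such knowledge plausible.

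The article does not show that enrolment has been or will be steered. The 2.2 to 5.5 points are not an expected bias: they need an assumed 0.1 to 0.25 SD shift, every known slot in both arms steered in the favourable direction, and no baseline adjustment. The change is still worth making, because selection at entry cannot be reliably undone afterwards and the article describes sampling as ongoing.

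**What to change.** For all remaining enrolment, amend Section 2.6:
- Replace the blocks of two by a list generated in advance for each stratum, with block sizes varying at random (for example 4 and 6) and not disclosed to recruiters.
- Have the list held by an existing team member who does not recruit, treat or analyse.
- Reveal each allocation only after consent and completion of the baseline questionnaires. This means reordering Section 2.10 and moving the first questionnaire in Table 1 ahead of allocation.
- Record the date of the switch, and state whether women enrolled before it were allocated as pairs already irrevocably enrolled.

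The cost is one list and a short amendment; N stays at 56. The downside is a larger possible imbalance within a stratum: at most 3 (half the largest block) instead of 1, so a worst case over six strata of 6 × 3 = 18 instead of 6 × 1 = 6. In the simulations the average difference in total arm size rises only from about 1.2 to 1.9, and its 95th percentile is 4 under both schemes. How many women remain to be enrolled, and so how much the change can still protect, is not stated.

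### In the protocol's worked example the block is drawn with Excel RANDBETWEEN after both women are known, and no sequence fixed in advance is described, so selection bias is avoidably possible

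*Protocol article*

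**What the plan says.** Section 2.6 (Random Allocation) stratifies the allocation "based on marital status (single and married) and BMI", the latter in three classes. Blocks have length two: "The two possible blocks are TC and CT, where T stands for the intervention group, and C stands for the control group". The generator is an Excel function: "Numbers will be generated randomly (with the RANDBETWEEN command in Excel software and ranges 1 and 2", with the key "for production number 1 CT block, for production number 2 TC blocks".

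The order of events appears only in an illustration. It opens with "For instance, two married women with a body mass index of 20–25 have been referred", and the draw follows: "assuming the number two is selected randomly. Therefore, these two people are assigned to the TC block". The first woman then takes the first place in the block and the second woman the other. Section 2.6 does not mention a list made before recruitment, say who makes the draw, or say what that person knows about the two women.

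Section 2.5.2 (Sampling) says that eligible, willing women "will be listed with a code (instead of specifications) in an Excel sheet". Section 2.9.2 mentions an unblinded coordinator, whose listed documentation duties do not include allocation. Section 2.16 (Limitations) mentions non-blinding and concealment of allocation from the researcher's side as a source of possible performance bias, in wording that can be read more than one way. The Consent section says that recruitment began in February 2023 and is still under way.

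**The concern.** Allocation protects against selection bias when whoever enrols or allocates can neither foresee the assignment nor influence it. A sequence fixed and locked beforehand achieves this, because once two women are on the list nothing remains to be decided. In the worked example the deciding number comes into being only after the pair and its stratum are known. RANDBETWEEN takes no seed from the user and returns a new value when the sheet recalculates. That is a property of the software, not a statement in the protocol. An unwelcome result could therefore be drawn again.

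This differs from the familiar weakness of blocks of two, where the second assignment can be guessed from the first. Repeating a draw would be possible with any block length, and having both women in hand before the draw does not prevent it.

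The matter counts more here because participants are not blinded (section 2.7) and the outcomes are self-reported (section 2.16), so the integrity of the draw carries much of the protection against bias. Section 2.11 also promises intention-to-treat analysis, which presupposes a well-defined randomised arm for each woman.

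**Working it through.** **The plan's own figures.** Section 2.5.1 gives means of 48.17 and 69.80, SDs of 20.61 and 23.38, type 1 error 0.05 and power 0.90.

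- Difference: 69.80 − 48.17 = 21.63.
- Common SD: √((20.61² + 23.38²)/2) = 22.04.
- The normal-approximation formula (two-sided) gives n = 21.8, so 22 per group and 44 in total.
- With 20% attrition: 44/(1 − 0.20) = 55, rounded to 56.

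The stated sample size reproduces, and nothing below alters it.

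**Number of draws.** There are 2 × 3 = 6 strata. One draw settles both women of a block, so 56/2 = 28 draws are needed if every block is filled.

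**Would a repeated draw be visible?** Either block gives one woman to each arm. Repeating a draw can only swap the two women of a pair, who share a stratum. Group sizes and balance on marital status and BMI class are the same whichever block is used, so neither check would reveal a repeat.

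**How much influence would a repeat give?** If someone prefers one order and may draw up to k times, the chance of reaching it is 1 − 0.5^k:

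| Draws allowed | Chance of the preferred order |
|---|---|
| 1 (honest) | 50% |
| 2 | 75% |
| 3 | 87.5% |
| 4 | 93.75% |

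The first row is the unbiased case.

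**Illustration in points, resting on assumptions.** The protocol gives no basis for a bias figure, so two quantities must be assumed: the correlation r between an operator's impression of a woman and her later resilience score, and the share q of pairs in which the draw is repeated until favourable, always in the same direction. The expected gap between two independent standard normal values is 2/√π = 1.128. The bias in the unadjusted comparison is then q × 1.128 × r × 22.04.

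- r = 0.3: q = 25%, 50% and 100% give 1.9, 3.7 and 7.5 points.
- q = 100%: r = 0.1 gives 2.5 points and r = 0.5 gives 12.4 points.
- One repeat only gives a 75:25 split, a net shift of 0.75 − 0.25 = 0.5, so half of each figure.
- q = 0 gives no bias.

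For scale, 7.5/21.63 is about a third of the planned difference. These figures show what the procedure would permit. They do not estimate what has happened.

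**The case against.** The strongest reply is that the text supports only a narrow point. The timing comes from one illustration; the general sentence gives none and would also fit numbers generated beforehand. A single honest draw is unbiased, and harm requires deliberate misconduct. Women are listed by code, which weighs somewhat against a draw made with their characteristics in view, although their stratum must be known. Resilience is measured before the intervention and enters the repeated-measures or mixed model (section 2.13), and confounders are examined (section 2.15), so selection on resilience would partly show at baseline. Drawing for a pair also leaves no second assignment to guess, an advantage that a careless remedy would lose. All of this stands, and it limits the point to an exposure.

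A reader might go further and infer that the spreadsheet keeps no fixed record, that later entries overwrite earlier draws, or that the intention-to-treat arm cannot be verified. The article does not support this. It does not say whether drawn values are frozen, written down or logged elsewhere, and does not link the coded list of women to the draw. A condensed article may leave such details to the full protocol. Only intervention women attend the six sessions, so some trace of actual group membership is to be expected.

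The reply does not account for the example itself. The authors chose to show a draw made after both women were referred, and the article nowhere describes a sequence fixed in advance that would contradict it.

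**Conclusion.** The point holds as an avoidable exposure to selection bias. As illustrated in section 2.6, the block is drawn after the pair is known, the draw can be repeated, and a repeat would leave group totals unchanged. One hidden repeat moves the chance of a preferred order from 50% to 75%. This rests on taking the worked example as the intended procedure and on the general behaviour of RANDBETWEEN. It does not show that any draw was repeated, that records are missing or that the comparison is biased. The point-bias figures depend wholly on an assumed correlation and assumed deliberate repetition, and should not be cited without those assumptions. The change is worth making because recruitment is ongoing and the safer method is cheap.

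**What to change.** For the remaining allocations:

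1. Generate the block sequence for each of the six strata once, with a seeded program or with RANDBETWEEN values pasted as fixed values. Date and lock the file, and keep it from those who enrol.
2. Log the IDs, stratum and order of both women before their block is released. Releasing the pair together keeps the second assignment unpredictable. If women must be released singly, use longer blocks of varied length; envelopes opened one at a time with blocks of two would make every second assignment predictable.
3. Confirm the arms of women already randomised from contemporaneous records, and use these as the intention-to-treat arms.
4. Reword section 2.6 to state this order of events, and report the change of method with its date.

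The cost is a short amendment and a small amount of preparation. Sample size and analysis are unaffected. Pairwise release means that a woman may wait for a second one in her stratum (at most six waiting at any time), as the worked example already implies. Women allocated before the change remain under the present method, which has to be reported.

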### Blinding

2.7

It will be impossible to keep participants blind during the intervention process, as a result of the nature of the intervention [44]. Blinding will be done at the assessor level [45]. In this way, after concluding the work, the research colleague hands over the questionnaires to the samples, and after completing the questionnaire, a box will be placed there, and the participants will put the completed questionnaire in the box. Groups are named A and B. The statistical analyst is also blinded, and at the end of the analysis, the coded groups will be identified [44, 45, 46]. Figure 1 is the CONSORT flow diagram and includes the calculation of the numbers of eligible, screened, enrolled, and analyzed participants.

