#### Data Collection Tools

2.9.1

In this study, the level of patient resilience will be measured as the primary outcome using the Connor‐Davidson Resilience Scale (CD‐RIS). The reliability and validity of the Persian Resilience Scale have been investigated and validated in preliminary studies in patient and normal samples. Mohammadi used Cronbach's alpha coefficient; the reliability scale reached 0.89, and the worth of each item alongside the overall score using the correlation coefficient ranged from 0.41 to 0.64 [47]. Samani and Sahragard, in a study on students in Shiraz, achieved scale reliability through Cronbach's alpha coefficient of 0.87 [48].

Additionally, the quality of life of the patients (as the secondary outcome) will be measured using the PCOS Health‐Related Quality of Life Questionnaire (PCOSQ). Amini et al. showed that the Iranian version of PCOSQ has acceptable validity and reliability and is an appropriate tool for measuring the quality of life of patients with polycystic ovary syndrome. To assess the reliability of the questionnaire, they employed the method of evaluating the internal consistency of the instrument. The findings demonstrate that the Cronbach's alpha coefficient for the entire questionnaire was 0.90, for emotional aspects it was 0.80, for hirsutism it was 0.87, for weight it was 0.77, for infertility issues it was 0.84, and for menstrual issues it was 0.52. In addition to testing the validity of the questionnaire, a type of validation, namely item‐level correlation and comparison between known groups, was used. So, each question shows the highest correlation coefficient with its relevancy domain, and all coefficients are greater than 0.4 [49].

Eventually, their anxiety and depression (as the secondary outcome) will be evaluated using the Hospital Anxiety and Depression Scale (HADS). Kaviani et al. showed in their research that the HADS scale and subscales of anxiety and depression have good validity, reliability, and internal consistency with a Cronbach's alpha coefficient of 0.07 for the seven items of the depression scale, and 0.85 for the seven items under the anxiety scale [50].

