#### Hypnotherapy Intervention Group

2.10.1

In the intervention group, hypnotherapy is performed by a qualified researcher who is certified by the Iranian Association of Clinical Hypnosis and holds a valid credential. For every participant in the intervention group, there will be 6 weekly hypnotherapy sessions lasting 40–60 min each (Table 1).

**Table 1 hsr271608-tbl-0001:** The content of six hypnotherapy sessions.

Sessions	The subject matter of the session
First	Taking a history, fully explaining how to do the work, educating and preparing the patient, eliminating the misunderstanding of hypnosis, and completing the questionnaires (Patients are also asked to describe a place in the real world that gives them a sense of safety and comfort).
Second	Induction and deepening, and direct instincts to increase relaxation and conditioning for rapid hypnosis in the next sessions.
Third	Strengthening the ego to increase self‐esteem and increase the endurance and resilience to life issues in the individual.
Fourth	Age regression and dealing with negative emotions, and then increasing calmness.
Fifth	Age progression and conditioning to improve lifestyle.
Sixth	Reviewing the previous sessions, the mental experience of a favorable physical feeling, and focusing on increasing relaxation in the whole body and mind. Completing the questionnaires again.

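### Section 2.7 claims assessor-level blinding, but every efficacy outcome is rated by women who know their arm, and the intervention arm's immediate post-treatment forms are completed within the sixth hypnotherapy session

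*Protocol article*

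**What the plan says.** Section 2.7 (Blinding) first concedes that "It will be impossible to keep participants blind during the intervention process". It then states that "Blinding will be done at the assessor level" and explains how: "after concluding the work, the research colleague hands over the questionnaires to the samples", and once the forms are filled in "the participants will put the completed questionnaire in the box". It adds: "The statistical analyst is also blinded, and at the end of the analysis, the coded groups will be identified".

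Section 2.9.1 says that "the level of patient resilience will be measured as the primary outcome using the" Connor-Davidson scale. It names two secondary instruments: the PCOSQ for quality of life and the HADS for anxiety and depression.

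Table 1 (Section 2.10.1) describes the sixth session as a review of earlier sessions, followed by "focusing on increasing relaxation in the whole body and mind. Completing the questionnaires again". Section 2.10.2 says that control questionnaires are done at the same time as those of the intervention group at every stage, and gives no setting for them.

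Section 2.16 (Limitations) acknowledges that "participants are aware they are engaging in an intervention entitled the Effect of Hypnotherapy on the Resilience of Women with PCOS" and that bias is probable. It also names reliance on self-report, possible performance bias, and a possible placebo effect from the greater staff contact in the intervention arm.

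**The concern.** There are two linked problems.

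- **The blinding label.** When an outcome is a self-completed scale, the assessor is the participant. Section 2.7 says that participants are unblinded, so it cannot also deliver assessor-level blinding for these outcomes. A reader who relies on that section when judging risk of bias would credit the trial with a safeguard it does not have, for the primary outcome and both secondary instruments.
- **The setting of the immediate score.** There are only two post-treatment measurements of resilience: right after the intervention and 4 weeks later. In the intervention arm the first is taken within a hypnotherapy session, straight after relaxation content. A short-lived post-session state could then be counted as a gain in resilience, in that arm only. Participant unblinding cannot be avoided in this trial. An unequal setting for the forms can be.

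**Working it through.** **Who rates each outcome**

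| Element | What the article gives | Blinded? |
|---|---|---|
| Participant | Cannot be blinded (2.7); knows the study title (2.16) | No |
| Resilience, PCOSQ, HADS | Questionnaires (2.9.1), completed by the participant (2.7); self-report conceded (2.16) | No |
| Colleague handing out forms | Not said to be unaware of allocation (2.7) | Not stated |
| Statistical analyst | Groups coded A and B (2.7) | Yes |

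No clinician-rated or objective efficacy outcome is named, so there is no outcome to which assessor blinding could apply. The collection box may limit staff influence and help keep the analyst masked. It does not mask the person who gives the answers. Section 2.16 discloses the bias but does not withdraw or qualify the statement in Section 2.7.

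**The conditions of the immediate score**

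- Intervention arm: forms are listed as the last item of session six, after the relaxation content (Table 1).
- Control arm: forms at the same time (2.10.2), with routine care and no hypnosis; setting not described.
- Timing is therefore matched. What precedes the forms is not.
- The 4-week questionnaires fall after the six sessions, so this second problem does not reach them. The first problem does.

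**The plan's own figure**

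The point does not depend on the sample size, but Section 2.5.1 supplies the scale of the primary outcome, so it was checked first.

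- Inputs: control 48.17 (SD 20.61), intervention 69.80 (SD 23.38), type 1 error 0.05 (taken as two-sided), power 0.90.
- Difference: 69.80 − 48.17 = 21.63.
- n per group = (1.960 + 1.282)² × (20.61² + 23.38²) / 21.63² = 21.8, so 22. This matches the article.
- Attrition: 44 / 0.80 = 55, rounded up to 56 for two equal groups. This matches too.
- Root-mean-square SD: √[(20.61² + 23.38²)/2] = 22.04.

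**Illustration only: what a differential shift would do**

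The document gives no size for any reporting or post-session shift, so the shifts below are assumptions and not estimates. The table gives the rejection rate of a two-sided 5% two-sample t-test with no true effect and SD 22.04.

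| Assumed shift between arms (points) | 22 per group | 28 per group |
|---|---|---|
| 2 | 6% | 6% |
| 5 | 11% | 13% |
| 8 | 22% | 27% |
| 10 | 31% | 39% |

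The consequence runs from negligible to serious over this range, and nothing in the article says where in the range the trial would lie. Blinding the analyst removes none of it.

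**The case against.** The strongest reply is that the article is already candid. Section 2.7 opens by saying that participants cannot be blinded and spells out what it means by assessor blinding. Section 2.16 then names awareness of the title, self-report, performance bias and placebo effect. On this view the fault is one mislabelled term. That stands in part: the article does not conceal the bias. It nevertheless keeps a statement that its own description contradicts.

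Several stronger readings are tempting, and the text does not support them:

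- *That Section 2.7 and Table 1 contradict each other on when the forms are given.* Section 2.7 has a colleague hand over the forms once the work is concluded. That can mean the end of session six, which fits Table 1. The passages are unclear together, not incompatible.
- *That the hypnotherapist is present while the forms are completed.* Table 1 lists completion as session content but does not say who is in the room or who gives out the forms.
- *That controls have no contact or session at all.* Section 2.10 (cosmetic procedures) and Section 2.15 (diet and exercise) refer to checks at each session in text about both groups. Controls may have some contact. What can be said is that they have no hypnosis and that their setting is not described.
- *That the bias has a known size or a certain direction.* An effect in favour of hypnotherapy is plausible, but the document establishes neither.

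A further reply is that right after the intervention is the declared time point and that a 4-week score is also planned. That is fair. The objection here is to the unequal conditions at that time point, not to having an early measurement.

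**Conclusion.** The point holds in two parts.

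1. The statement of assessor-level blinding is wrong for every named efficacy outcome at every time point. This follows directly from Sections 2.7, 2.9.1 and 2.16 and needs no assumption beyond the outcomes being those listed. Only the analyst is blinded.
2. The immediate post-intervention score may include a transient post-session state in the intervention arm only. This rests on Table 1 as written and on the absence of hypnosis in the control arm. Its size is unknown.

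The sample size is unaffected. The 4-week score avoids the session effect but remains unblinded self-report, so it is less affected and not clean. Correction is worthwhile because the label is plainly inaccurate and the unequal setting is avoidable at modest cost.

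**What to change.** - Reword Section 2.7 along these lines: *Open-label; all efficacy outcomes are participant-reported and not blinded; only the statistical analyst is blinded (groups A and B).* Keep the box procedure, described as a way to limit staff influence on the answers.
- For women still to be assessed, take the post-intervention questionnaires out of session six. Have both arms complete them in the same short window and the same setting, given out by the research colleague and away from the hypnotherapist. State that setting for each arm.
- Apply the change to both arms at once and record it as a dated amendment with Ethics Committee approval, as Section 2.12 requires.
- Interpret the immediate score with this caveat. Report that the 4-week score avoids the session effect but is still unblinded self-report.

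**Cost.** The rewording costs nothing. Moving the forms brings slightly more risk of missing questionnaires than completion in the session, and needs an ethics amendment. The Consent section says that sampling began in February 2023 and is ongoing, so the change would also leave two measurement conditions for this time point within one trial. The amendment date should be kept in the data so that the two can be told apart.
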